**Box 1. Features of organisational change champions identified by [name] et al (2012) (44)**

- Has authority to cultivate an environment for ongoing practice improvement/organisation learning
- Has a clear vision for the larger organisation and effectively communicates how the project-based innovation fits into that vision
- Ongoing role
- Actively and enthusiastically promotes both the specific project as well as ongoing practice improvement
- Mobilizes resources (internal/external) for ongoing practice improvement
- Navigates the socio-political environment for ongoing practice improvement
- Provides leadership for ongoing practice improvement

702

703 Change champions will attend 2-day training at their own site aimed at tailoring the intervention to  
704 local needs and contexts. Champions will be supported and trained to administer the audit tool to  
705 identify strengths and weaknesses at their centre against recommendations in the guidelines. They  
706 will also be trained to identify barriers and facilitators to cancer pain management and helped to  
707 develop solutions. They will be trained in the use and trouble-shooting of the pain screening system.  
708 Finally, they will be trained to provide information to patients and train them in using the patient-  
709 held resources, as well as to induct new staff into use of the guidelines at their centre.  
710

711 Also during the training period, all clinical and front of house administrative staff will attend a half-  
712 day workshop at their centre in which they will be given an overview of the guidelines, summary  
713 clinical pathway and implementation resources by the change champions at their site with support  
714 from the project team. Medical and nursing teams will undergo online training in pain assessment  
I001/ 4th September, 2018

715 and management via QStream modules to assess their understanding of recommendations in the  
716 guidelines.

717

718 During the *intervention phase*, the process for feeding back individual patient results from  
719 screening will be monitored, with medical teams receiving a summary report of screening data for  
720 each patient prior to consultation to inform management, and a copy filed in the medical record.  
721 The process by which this happens will vary by centre and can be electronic (e.g. email) or hard  
722 copy (automatic print-out, carried into the consultation by the patient or administrative staff).  
723 Adherence to standards of pain screening, assessment and management will be monitored via the  
724 audit tool. Feedback will be at the centre level rather than refer to any individuals, and data will be  
725 recorded and fed back in such a way that no individual can be identified. Health professionals  
726 selected to undertake audits will do so under the supervision of a project team member until the  
727 latter is satisfied they are able to conduct audits to the standard required. Future audits will be  
728 observed periodically throughout the study. Health professionals conducting the audits will be  
729 invited to engage in open communication with the project team at any time. Patients will be  
730 provided with patient-held resources and brief (5 minute) training on how to use them. Resources  
731 will include a pain diary, personal goal setting support, a tool for monitoring capacity to self-  
732 manage pain and identify related needs and a pain management plan detailing medications and out-  
733 of-hours contacts. The degree to which champions take on all responsibilities or delegate these to  
734 other staff who they train in carrying out relevant tasks will be tailored to the individual site. Those  
735 rolling out the intervention at each centre will be invited to participate in regular teleconferences  
736 with staff at similar sites and members of the project team to share learning and solve problems.

737

738 During a *sustainability phase*, site specific health professionals who are trained in the use of the  
739 audit tool will provide the research team with de-identified audit feedback data on patients screened  
740 as having a severe pain score  $\geq 7$  NRS to assess whether adherence to standards of pain screening,  
741 assessment and management have continued.

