## BACKGROUND AND RATIONALE

### 1.1 Review of the literature

In 2007, 339,000 Australians – or 1.6% of the population - had been diagnosed with cancer within the last 5 years (8). As cancer treatments evolve, those who previously would have died within months are now living with cancer as a chronic condition often in addition to other co-morbidities, with a heavy burden of physical and psychological symptoms (9). Most people with advanced cancer, in particular, present with symptoms related to both cancer and its treatment (10). Symptoms also impact on informal carers, with an estimated 2.6 million Australians providing home care to someone affected by illness or disability, many of whom have cancer.

Pain is experienced by 30-75% of people with cancer and is rated as moderate-severe by 40-50% and severe by 25-30% (11). Studies show that up to 42% have inadequate analgesia (12). Undertreated pain not only reduces patient quality of life (QOL) but also increases health service use, impacts on carers and, at a societal level, reduces the ability of patients and carers to participate actively in employment and other activities. A wealth of literature highlights barriers to pain assessment and management at the levels of patients (e.g. reluctance to report pain, misconceptions regarding opioids), health professionals (e.g. lack of time and expertise) and the healthcare system (e.g. lack of coordination and timely access to analgesia) (13-18). Patients from non-English speaking backgrounds are likely to suffer especially poor levels of care because they are less able to communicate their needs and navigate the healthcare system (19). Patients in regional and rural areas may also not receive the same standard of care as those in metropolitan areas (20), despite the fact that minimum standards for pain assessment and management can be readily achieved without input from specialist services in the overwhelming majority of cases where pain is not complex. These standards include routinely screening and assessing pain, providing patients with pain self-management strategies, ensuring availability of regular and breakthrough analgesia, and offering laxatives to patients receiving opioids (21). Studies have shown that implementation of evidence-based clinical practice guidelines for pain recommending these standards can improve the processes of care and patient outcomes (22).

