#### 5.1.2.1 Consent process

This study will use four procedures relating to consent:

1. A waiver on patient consent to use de-identified screening and audit data for endpoints comparing average pain and adherence to key standards of cancer pain assessment and management within the patient population during intervention and sustainability versus control periods;
2. An opt-out procedure for patient permission to obtain their contact details to telephone them 1 week later about the research for the primary outcome of worst pain on a 0-10 NRS 1 week after a positive screen. Upon contact, patients will be invited to give verbal consent to provide primary outcome data but will still be at liberty to refuse at that time;
3. A verbal informed consent procedure for secondary outcome data (surveys, interviews and medical record audit);
4. A written informed consent procedure for involvement by patients in the study's health economic evaluation.

The National Health and Medical Research Council (NHMRC) National Statement on Ethical Conduct of Research (2007) includes provision for waiving and an opt-out approach to consent in Chapter 2.3 (45).

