### 1105 5.2.4.4 Patient-level process measures

1106 Number and duration of consultations, multi-disciplinary input, primary care support, and standards  
1107 of care recommended by the guidelines. Items of particular interest will be instances of screening,  
1108 assessment, patient education, regular analgesia (agent, route, dose), breakthrough analgesia (agent,  
1109 route, dose, and number of times taken) and management of side-effects (preventative and  
1110 treatment), as well as any other anti-cancer, interventional and non-pharmacological methods used  
1111 to address pain. The clinical audit tool (administered by research assistants to standardise between  
1112 conditions/centres), will assess participants' clinical records retrospectively. Because it is often not  
1113 documented in medical records, patients' receipt (or otherwise) of pain education will be measured  
1114 by asking the patient at each time-point for telephone follow-up.

1001/ 4th September, 2018

1115 **5.2.5 Descriptive/control variables**

1116  
1117 **5.2.5.1 Patients**

1118 **5.2.1.1.1 Demographics**

- 1119 1. Age  
1120 2. Gender  
1121 3. Availability of an unpaid carer:  
1122 a. lives with carer  
1123 b. lives alone but carer available  
1124 c. lives with non-carer  
1125 d. lives alone, no carer  
1126 4. Postcode  
1127 5. Country of birth  
1128 6. Language spoken at home  
1129 7. Aboriginal and/or Torres Strait Islander status

1130 **5.2.1.1.2 Cancer diagnoses**

1131 The following clinical data will be collected:

- 1132  
1133 i. Site  
1134 ii. Tumour stage  
1135 iii. Sites of metastases  
1136 iv. Time since diagnosis  
1137 v. Current treatment

1138 **5.2.1.1.3 Comorbidities**

1139 Comorbidities will be identified that influence pain or its management according to the guidelines.  
1140 Conditions of interest will include painful conditions (e.g. arthritis), renal impairment, gastro-  
1141 intestinal ulcers and conditions causing cognitive impairment (e.g. dementia).

1142 **5.2.1.1.4 Performance status**

1143 Performance status will be measured using whatever tool is routinely in practice at each site. It is  
1144 anticipated that these will most often be the Karnofsky Performance Status (KPS) (54) or Australia  
1145 - modified Karnofsky Performance Status (AKPS) (55) at palliative care sites and the Eastern  
1146 Oncology Cooperative Group (ECOG) Performance Status (56) at oncology sites. Conversion  

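### The sustainability audit samples only patients already screened at NRS 7 or more, so it cannot show whether outpatients are still being routinely screened

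*Protocol*

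**What the plan says.** Protocol 4.1.2 describes the sustainability phase in one sentence, which fixes both the sample and the purpose of the audit.

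- **Sample:** site staff trained in the tool send data "audit tool will provide the research team with de-identified audit feedback data on patients screened" "as having a severe pain score" of at least 7.
- **Purpose:** "NRS to assess whether adherence to standards of pain screening", and to the later steps of assessment and management, has been kept up.

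Section 1.1 says what the screening standard is: "These standards include routinely screening and assessing pain". This is a standard about how many attending patients are screened.

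Three other places bear on the point.

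- For the intervention phase, 4.1.2 says: "Adherence to standards of pain screening, assessment and management will be monitored via the" audit tool. It does not state which patients are audited.
- Section 5.2.4.4 lists patient-level process measures, with standards "of care recommended by the guidelines. Items of particular interest will be instances of screening". These are read retrospectively from participants' clinical records: "The clinical audit tool (administered by research assistants to standardise between" conditions and centres.
- The consent waiver in 5.1.2.1 covers de-identified screening and audit data for comparing average pain and "adherence to key standards of cancer pain assessment and management within the patient population during intervention and sustainability versus control periods".

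**The concern.** Being screened is the condition for entering the audit, and continued screening is one of the things the audit is meant to judge. If a centre stopped screening most of its outpatients, the few still screened with severe pain would form the whole audit sample, and each of them would have been screened. The missed patients would leave no trace.

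The sustainability phase has its own place in Figure 1, and section 3.5 counts assessment of sustainability among the advantages of the design. The audit is the only sustainability measure that 4.1.2 describes. A statement that screening adherence continued, drawn from it, would have no support as a statement about coverage. Such a statement could feed the account of mechanisms (objective 4 in 2.2.2) and the dissemination planned in 1.4.

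**Working it through.** The protocol gives no audit size, screening rate or coverage target, so there is no figure to reproduce. The check is one of logic, with an illustration on assumed numbers.

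**Step 1. The two quantities.** Let N be eligible outpatients attending in a period, c the proportion screened, and p the proportion of screened patients scoring 7 or more.

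- Coverage, which is what the standard in 1.1 concerns: (N × c) / N = c.
- Patients in the audit: N × c × p.
- Share of audited patients who were screened: (N × c × p) / (N × c × p) = 1, for any c above zero.

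The last quantity does not depend on c.

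**Step 2. Illustration.** Assumed, not from the protocol: N = 500, and p = 10% or 25%.

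| Coverage c | Screened (500 × c) | Expected audited, p = 10% | Expected audited, p = 25% | Share of audited who were screened |
|---|---|---|---|---|
| 100% | 500 | 50 | 125 | 100% |
| 80% | 400 | 40 | 100 | 100% |
| 50% | 250 | 25 | 62.5 | 100% |
| 20% | 100 | 10 | 25 | 100% |
| 5% | 25 | 2.5 | 6.25 | 100% |

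The number audited does fall with coverage, but it cannot be read back. An expected 25 audited patients arises from 50% coverage with p = 10%, and equally from 20% coverage with p = 25%. A change in N would confuse it further.

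**Step 3. Does another section supply the missing denominator?**

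- The Participant Master Index (5.1.1.1) holds only patients who screen at 2 or more.
- The screening spreadsheet (5.1.2.2) holds patients who were screened. It could give a numerator but has no count of attenders, and 4.1.2 does not say it runs on into the sustainability phase.
- The waiver (5.1.2.1) permits use of screening data across periods. The adherence endpoint it names concerns assessment and management, and it gives no attendance count.
- Centre-level process measures (5.2.4.2) include adherence to the guidelines, without a sample or denominator.
- The participant audit (5.2.4.4) reads the records of people who entered the study through a positive screen (3.2.1), so it cannot measure coverage either.

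None of them closes the gap.

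**The case against.** The strongest reply is that the audit tool is an existing external instrument (1.2) whose items are not reproduced. Its screening items need not ask whether the patient was ever screened. They may ask whether the score was documented or whether screening was repeated. In the intervention phase, 4.1.2 has a summary report sent to the medical team before the consultation and a copy filed in the record, and a screened patient can fail on such items. This stands: the audit can say something about how completed screens were handled. It does not restore coverage, because unscreened attenders are still absent.

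A reader might infer more than the text supports.

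- **That 5.2.4.4 has the identical fault and always returns 100%.** It counts recorded instances of screening. Eligibility comes from the screening form, not the clinical record, so the recorded count can be zero, one or several. It fails as a coverage measure but is not a constant.
- **That the intervention-phase audit is affected too.** Its sample is not stated, so nothing can be concluded about it.
- **That the trial would report equal screening in the control and intervention phases.** The cross-period adherence endpoint in 5.1.2.1 names assessment and management, not screening, and no such screening comparison is planned.
- **That screening is the step most likely to lapse.** The protocol does not say so.

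It is also fair that sustainability has no objective of its own in 2.2, and that the primary outcome, power and cost-effectiveness analysis do not depend on this audit.

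**Conclusion.** The concern holds for the sustainability audit in 4.1.2. As written, its sample cannot show a fall in the proportion of outpatients screened, whatever the size of that fall and however many records are audited. This follows from the sample definition and needs no assumption about rates; the table only illustrates it. It does rest on reading the screening standard as routine screening of attending patients, which is how 1.1 puts it.

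A statistical analysis plan could not repair this, because it cannot recover attenders who were never counted.

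The scope is limited. The conclusions on assessment and management remain usable for the severe-pain patients sampled, as does any conclusion on documentation or repetition of completed screens. The point affects one process conclusion about sustainability and should be corrected before that conclusion is drawn.

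**What to change.** In 4.1.2, state that the audit of screened patients supports conclusions on assessment and management, and on documentation of completed screens. Then do one of two things:

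1. Drop screening adherence as a sustainability conclusion. This costs one amended sentence.
2. Measure it separately as patients screened divided by outpatient attendances, per centre and per period, with numerator and denominator in the same unit (patients or visits). The intervention period needs the same count, since continuation can only be judged against an earlier level.

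Add to 5.2.4.4 that its count of recorded screening instances is not a measure of coverage.

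The second option needs one attendance count per centre and period from the appointment system. It has two downsides. Appointment lists include patients without active cancer, which 5.1.1.1 has treating clinicians identify, so the denominator is approximate. And because the protocol does not say that the screening spreadsheet runs in the sustainability phase, the numerator may also be new collection there.

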## 742 **4.2 Concurrent treatments**

743 Trial patients will continue their usual treatment regimen in all respects other than those prescribed  
744 for cancer pain when in the intervention period.

## 745 **4.3 Post study treatments**

746 All participants will be followed by their clinician for continuing care, irrespective of the point at  
747 which they exit the study.

# 748 **5.0 Study procedures**

## 749 **5.1 Identifying and recruiting participants during intervention** 750 **period**

### 751 **5.1.1 Patients**

#### 752 **5.1.1.1 Identification of potential participants**

753 All patients screening  $\geq 2$  NRS for worst pain of any cause at oncology centres who have current  
754 active cancer as identified by treating clinicians will be eligible for inclusion in components of the  
755 study examining secondary outcomes, although only patients screened with worst pain  $\geq 5$   
756 (moderate-severe) will have data included in the primary analysis. Eligibility for components of the  
757 study focusing on secondary outcomes will be screened by a research assistant against other criteria  
758 on initial approach.

759

760 The screening form will give patients an opportunity to opt out if they do not wish to be contacted  
 761 (see Appendix 2 for wording). The project team will extract contact details for patients scoring  $\geq 2$   
 762 on a 0-10 NRS who do not opt out. All participants who score worst pain  $\geq 5$  on a 0-10 NRS who do  
 763 not opt out will be contacted either in person at the centre or via telephone and invited to give  
 764 verbal consent to rate their pain a week later for the primary outcome. Where screening data  
 765 indicates that the patient chose to complete measures in a language other than English, healthcare  
 766 interpreters will be employed to translate the verbal consent and data collection exchange between  
 767 the research assistant and the patient. (Appendix3). Additionally, recruitment to research aimed at  
 768 answering secondary objectives of the project relating to pain, empowerment, QOL and cost  
 769 effectiveness and the qualitative sub-study will occur by approaching patients who score 2 or more  
 770 on a 0-10 NRS at the centre or by telephone. Where patients cannot be approached at the centre, the  
 771 team will telephone the patients to ask if they are interested in learning more about the study and  
 772 seek their informed consent to participate. A cover letter, two copies of the participant information  
 773 and consent forms will be posted out together with copies of the questionnaires and a reply-paid  
 774 envelope. See Figure 2 and 3 for flow diagrams of recruitment of patients to primary and secondary  
 775 outcome components respectively.

776

777 A Participant Master Index (an excel file to track participant ID numbers and progress through the  
 778 study) will be kept of all patients who screen  $\geq 2$  NRS for worst pain including the reasons for non-  
 779 entry regarding failure to meet inclusion criteria and refusal.

780

[figure not shown]

802 *NOTE: The above flow in patient recruitment and data collection occurs regardless of whether the*  
 803 *centre is in the control or intervention arm.*

804

805 **5.1.2 Figure 2: Study diagram of patient recruitment and data collection for**  
 806 **primary endpoint of worst pain at 1 week after positive screen**

[figure not shown]

845 **5.1.2 Figure 3: Study diagram of patient and carer recruitment and data**  
 846 **collection for secondary outcomes**

847  
 848 *NOTE: The above flow in patient recruitment and data collection occurs regardless of whether the*  
 849 *centre is in the control or intervention arm.*  
 850

ABBREVIATIONS: EORTC QLQ C15-PAL = European Organisation for the Research and Treatment of Cancer Quality of Life Questionnaire C15-Palliative care; MBS = Medicare Benefits Scheme; NRS = numerical rating scale; PBS = Pharmaceutical Benefits Scheme

#### 5.1.2.1 Consent process

This study will use four procedures relating to consent:

1. A waiver on patient consent to use de-identified screening and audit data for endpoints comparing average pain and adherence to key standards of cancer pain assessment and management within the patient population during intervention and sustainability versus control periods;
2. An opt-out procedure for patient permission to obtain their contact details to telephone them 1 week later about the research for the primary outcome of worst pain on a 0-10 NRS 1 week after a positive screen. Upon contact, patients will be invited to give verbal consent to provide primary outcome data but will still be at liberty to refuse at that time;
3. A verbal informed consent procedure for secondary outcome data (surveys, interviews and medical record audit);
4. A written informed consent procedure for involvement by patients in the study's health economic evaluation.

The National Health and Medical Research Council (NHMRC) National Statement on Ethical Conduct of Research (2007) includes provision for waiving and an opt-out approach to consent in Chapter 2.3 (45).

#### 5.1.2.2 Waivered consent

A waiver on consent will be sought to use pain screening data to compare patient populations between centres at baseline and to see whether this population is changed in terms of pain by the intervention. As well as screening data, a waiver on consent will be requested to collect data on age, gender and cancer type to contextualise screening data, compare patient characteristics between centres and establish the representativeness of samples for primary and secondary outcome assessment. These data will be extracted by local staff or project staff. Screening measure data will be entered onto an Excel spread-sheet by local or project staff. For patients who score  $\geq 2$  and who do not opt out, their name and contact details will be entered onto the spread-sheet. Names and contact details for those patients who score NRS 0-1 for worst pain or who opt out of being contacted will not be entered onto the spread-sheet.

